### Composite of SS

Because SS are mutually reinforcing systems (19), we plan to create a substance use-relevant SS composite to represent how these SS co-occur. To select a set of specific stressors to create a substance use-relevant SS composite, existing empirical data supporting the relevance of individual- or area-level social stressors for substance use, when possible, in adolescence was examined. Specifically, lower childhood socioeconomic status is associated with increased risk for substance use disorders (109, 110). Adolescents from low-income families living in high income neighborhoods were at greater risk for smoking compared to adolescents from low-income families living in low income neighborhoods, and compared to adolescents from high-income families (111). Youth who drop out of high school are more likely to engage in substance use or misuse and to meet criteria for substance dependence compared to their peers who stay in high school (37, 112, 113). Increased perception of neighborhood violence and exposure to violence is associated with increased substance use (38, 114). Other social factors considered for the SS composite were less consistently associated with substance use risk. For example, while residential segregation has been consistently associated with differential access to substance use treatment (115, 116), the relationship between segregation and substance use risk is less clear (117, 118). Similarly associations with access to green spaces and substance use risk have been found to have a less consistent relationship with substance use (119). Therefore, generating a composite of SS using census tract level group differences in income, educational attainment, and precinct level murder rates as indices will provide a measure of SS that is relevant for adolescent substance use risk.

### Measurement of SS

To determine the role of SS on substance use risk in adolescents, we will create a composite measure of substance use-relevant SS. This composite will be based on area-level racial group differences in income, education, and exposure to violence, as exposure to lower levels of income and education, and higher levels of violence have been related to increased risk for substance use (2–9). To calculate SS SU-relevant measures of income and education, we will use the Index of the Concentration at the Extremes using income and education, using data from the US census. For example, for income, within each census tract (i) our participants live in, the ICE_income_ will be calculated as the number of White individuals in the top income quintile (Ai) minus the number of racially minoritized individuals in the bottom income quintile (Pi), divided by the total population across all income quintiles (Ti; Figure 2).

**Figure 2 F2:**
[figure not shown]
The ICE formula, from Krieger et al. (22).

Previous studies report a relationship between ICE_income_ and a wide array of health disparities including infant mortality, child mortality, premature mortality, and exposure to black carbon, and it has been effectively used in small geographical units, including at the census tract level (21, 22, 120). ICE_education_ will be calculated within each census tract (i) our participants live in as the number of individuals 25 years or older (Ai) with 4 years of college or more who are White, minus the number of individuals who did not finish high school who are racially minoritized, divided by the total population across all education levels.

Previous analyses of socioeconomic factors in our BYS sample have demonstrated variation in both within and across sites, supporting our ability to examine the research questions described here. For example, within the continental US BYS sample, 56.7% of participants at the young adult assessment reported meeting the federal poverty threshold during young adulthood, while the remaining 43.3% reported not meeting this threshold (108). In the continental US 59.3% of the mothers of our participants had obtained a high school diploma or GED, again demonstrating variation among our sample. In PR, 65.0% of participants met the poverty threshold, and 80.8% of the mothers of our participants had done so in PR (108), demonstrating variation within the PR sample, and across the two sites of the BYS.

Disparities in exposure to violence will be measured using differences between the number of murdered White individuals and the number of murdered minoritized individuals at the precinct-level, divided by the total precinct population. In the continental US, these data can be obtained via requests to the National Crime Victimization Survey (NCVS), the primary source of national data on criminal victimization, at the precinct level. Crime data for PR is reported through the Uniform Crime Report (UCR) Program through the Government of Puerto Rico. This measure is distinct from measures that capture, for example, individual direct experiences of violence, or area-level measures that reflect the presence of violence in a certain neighborhood, rather, the proposed measure captures the extent to which, at the area-level, one group is exposed to violence compared another group. Using a composite of these SS indicators, we aim to generate preliminary support for the hypothesis that SS will relate to neurocognitive mechanisms of substance use risk.

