### Statistical analyses

We will use generalized linear models (GLMs) using the SS composite variable as a predictor and brain structure in prefrontal regions of interest, DD-performance, neural correlates of DD performance and BJW as outcome variables. These GLMs will also control for family SUD factors, individual experiences of unfair treatment, age, sex, and the presence of a psychiatric diagnosis. Due to the importance of understanding SS alongside other negative exposures, our models will also include adverse childhood experiences, measured using a combination of parent and child report, gathered by interview.

Exploratory analyses will examine the role of each individual SS index on gray matter volume (e.g., the effect of area-level group differences in income alone) and will examine site differences (South Bronx vs. Puerto Rico) in the associations. Site differences may suggest site-specific approaches to prevention and intervention.

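### The violence component counts murder victims but names a victimization survey as its South Bronx source; Puerto Rico uses crime reports, so the component may not be comparable across sites

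*Protocol article*

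**What the plan says.** Under Measurement of SS, the Protocol article defines the violence component as "differences between the number of murdered White individuals and the number of murdered minoritized individuals at the precinct-level, divided by the total precinct population". The next sentence gives the source of those counts for New York: "In the continental US, these data can be obtained via requests to the National Crime Victimization Survey (NCVS"), which it goes on to describe as "the primary source of national data on criminal victimization, at the precinct level". For the other site it says "Crime data for PR is reported through the Uniform Crime Report (UCR) Program through the Government of Puerto Rico".

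Composite of SS confirms that murder is the intended quantity. It speaks of "generating a composite of SS using census tract level group differences in income, educational attainment, and precinct level murder rates as indices".

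Statistical analyses makes the composite the predictor for every outcome: "We will use generalized linear models (GLMs) using the SS composite variable as a predictor". On adjustment it says "These GLMs will also control for family SUD factors, individual experiences of unfair treatment, age, sex, and the presence of a psychiatric diagnosis", and a further sentence adds adverse childhood experiences. Site is not listed. It appears only in the exploratory paragraph, where the analyses "will examine site differences (South Bronx vs. Puerto Rico) in the associations".

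**The concern.** Two things are wrong or at risk.

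- **The source does not fit the quantity.** The component counts people who were murdered, and the New York source is a survey of victimization. A murder victim cannot answer a survey, so the source as named cannot be where the numerator comes from.
- **The source type is split by site.** New York has a survey and Puerto Rico has reported crime. If the two systems count differently, the difference lines up perfectly with site.

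The composite is the only predictor of interest for all three hypotheses, and progression to the next phase rests on an association above r = 0.30 for any one of them. A component that mixes measurement system with site could add a spurious contribution to that association or dilute a real one. The exploratory analyses of single SS indices on gray matter volume would use the violence index alone, so the other two components would not dilute a source difference there.

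**Working it through.** The article states no figure for this point, so there is none to reproduce. The check is a reading of the text, followed by an illustration for scale.

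**Step 1: components and sources.**

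| Component | South Bronx | Puerto Rico |
|---|---|---|
| Income | US census | US census |
| Education | US census | US census |
| Violence (murder victims by race) | Victimization survey | Crime-report programme |

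Violence is the only component whose source type changes with site.

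**Step 2: how many children.** Participants plans 72 children, half from each cohort: 72 × 0.5 = 36 per source.

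**Step 3: what could happen to the New York data request.**
- The survey yields no murder counts. The component is then missing for the South Bronx, or a substitute is chosen later that the plan does not name.
- The survey yields some other measure of victimization. The component is then a different quantity at each site.
- The request in practice leads to homicide records. The wording is then wrong, and comparability depends on whether those records match Puerto Rico's in years, area unit and race categories.

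The plan as written needs correcting in each case. A source offset enters the composite only in the second and third cases, or in the first if a substitute is used.

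**Step 4: illustration for scale, not an estimate.** These assumptions are not in the article: the violence index is z-scored over both sites together; the composite is an equal-weight mean of three indices; the other two indices do not differ by site; within-site correlations between indices are ρ = 0 to 0.5; the source offset between sites is d within-site SDs.

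- Share of the violence index's variance that is source artefact: b = (d²/4) / (1 + d²/4).
- Correlation of composite with site: √(b / V), where V = 3 + 2ρ(1 + 2w) and w = 1/√(1 + d²/4).

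| d | b | Composite–site correlation (ρ = 0.5 to ρ = 0) |
|---|---|---|
| 0.5 | 0.0625/1.0625 = 6% | 0.10 to 0.14 |
| 1 | 0.25/1.25 = 20% | 0.19 to 0.26 |
| 2 | 1/2 = 50% | 0.30 to 0.41 |

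If the composite were related to an outcome only through site, the unadjusted correlation induced would be the composite–site correlation times the site–outcome correlation. At d = 1 it could not exceed 0.26. At d = 2, reaching 0.30 would need a site–outcome correlation between 0.30/0.408 = 0.74 and 0.30/0.304 = 0.99. Under these assumptions, a source artefact of this size is unlikely to cross the progression threshold alone. It could still add to or mask an association.

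**The case against.** The strongest reply has four parts.

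- **The wording is permissive.** The text says where data can be obtained and is not an extraction specification, and an article condenses a fuller protocol. Condensing explains what is left out, however, and here a source is named that does not fit. The point stands.
- **One quantity is defined for both sites.** Two sources for one defined count create a risk of difference and do not prove one. This is correct. A reader might infer that the component is definitely not comparable, but the article supports only that it may not be.
- **Precinct-level counts.** A reader might also infer that a national survey cannot give figures for a single precinct. The article gives no survey design details, and its own text says the data are available at that level. That argument would need outside knowledge and is not relied on here.
- **The damage is limited and partly visible.** Only one of three components is affected, the study is an exploratory pilot, and site differences will be explored. All true. Standardising within site, or adding a site term, would remove a mean offset. Neither would produce murder counts from a survey of victims, and a site term would not correct a difference in scale.

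The absence of a site term is also an issue in its own right. It is cited here only because it is the route by which a source difference would reach the main results.

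**Conclusion.** The point holds. The named New York source does not fit a count of murder victims. That follows from the article's own definition of the component and its own description of the source. The source type differs by site with no harmonisation described, so one of three components, with 36 of 72 children on each source, may not be comparable. With no site term among the listed main-model covariates, any source difference would act as a site difference in the composite.

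The size of any bias cannot be computed from the article. It gives neither the offset between sources nor the weighting or standardisation of the composite, so the figures in the illustration rest wholly on assumptions. Nor does the article support the conclusion that the violence component must be dropped: Composite of SS argues for it from the literature, and removing it would change the construct.

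**What to change.** In Measurement of SS, replace the survey with police-recorded (crime-report type) homicide counts by victim race for the South Bronx. State that they match the Puerto Rico source in type, calendar years, area unit and race categories.

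If matching counts cannot be had at both sites, decide and record before analysis how the violence component will be handled. One option is a sensitivity analysis with the composite excluding it, reported beside the main result.

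The cost is a different data request and a few sentences of text. Nothing changes for participants.

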### Participant assessments

Interviews of parent and child participants, and MRI scans of children will collect data using the following methods:

#### Assessment of belief in a just world

Learning to wait for larger, later rewards is theorized to develop alongside, and in conjunction with a BJW (65). We will use the 13 item self-report Belief in a Just World scale, which uses a Likert-type scale, and has been previously used with adolescent populations (121, 122). This scale, as a whole, has a Cronbach's alpha of 0.827, which is considered good internal consistency, indicating high reliability (121).

#### Assessment of collection of MRI data

Children will be introduced to scanning protocols in a mock scanner session and encouraged to finish participation through frequent praise and reminders to respond to the task, and to stay awake during the resting state scan. Multimodal MRI scanning will include a structural MRI (~5 min) and DD task (~10 min).

#### Assessment of DD behavior and neural correlates

We will use an fMRI-adapted DD task previously used with adolescents to collect a DD performance and related brain activity. This task has good test-retest reliability for behavior and neural response (123). Like other monetary DD tasks, on any given trial, participants are asked to decide between a smaller sooner reward, or a larger later reward. Participants will first perform a calibration task comprised of 50 trials to assess each individual child's discount parameter *k* outside of the scanner. This discount parameter is used to create 90 trials presented in the scanner, in which the participant can be expected to choose the smaller, sooner reward half of the time, providing adequate data to examine neural response to smaller soon and larger later rewards. Participants are told that they will be paid the amount of one of their choices after the task is completed.

#### Scanning parameters

At both sites, we plan to collect data using a 3T MRI scanner, using a 64-channel coil. For structural scans, a T1-weighted magnetization-prepared rapid acquisition with gradient echo (MPRAGE) sequence will be collected (TR = 1,900 ms, TE = 2.26 ms, FOV = 256 × 256 mm, 176 slices, 1 × 1 × 1 mm^3^ voxel size, flip angle = 9°). For functional, task-based imaging, a gradient-echo T2^*^-weighted EPI sequence (TR = 2,000 ms, TE = 25 ms, 2 × 2 × 2 mm^3^ voxel size, xflip angle = 80°) will be collected.

#### Assessment of covariates: familial SUD risk factors

To control for familial risk, we will use data collected about one of the parents of the participant during Waves 1–3 of the BYS. More specifically, we will account for (1) parental sensation seeking during childhood/adolescence (depending on the age of the parent when they participated in BYS), captured by the Sensation Seeking Scale for Children (124); (2) parental impulsivity symptoms during childhood/adolescence (ADHD via DISC-IV) (125); (3) substance use and SUD status during childhood/adolescence (DISC-IV) (125); and (4) parental SUD during young adulthood, as measured by the CIDI (126).

#### Assessment of covariates: unfair treatment

This study is focused on the role of SS, which can operate outside of an individual's perception of unfair treatment. Therefore, to isolate the role of SS from the role the perception of unfair treatment due to race or ethnicity, we will control for experiences of ethnoracial discrimination using the Perceptions of Racism in Children and Youth Scale (PRaCY), a 10-item child self-report scale (127). The PRaCY has strong internal consistency reliability, and confirmatory factor analysis of the scale demonstrates good fit.

#### Assessment of additional covariates

Other covariates of interest also include age, sex, and psychopathology (DISC-IV, for consistency with assessment of the parental generation (125), and the CBCL/6-18) (128). Since ADHD medication are prescribed to more children in the US than any other class of medication (129), and since ADHD medication has been shown to impact neural activity (130), analyses of neural data will take into account ADHD medication, which is reported on the DISC (125).

#### Procedures

The proposed pilot study will not be advertised or publicized, rather, we will reach out to families who have participated in BYS to determine eligibility for the current study.

#### Power analysis

Since R61 grants are awarded to conduct exploratory research focused on establishing a proof of concept, the power analysis for this R61 will focus on effect size rather than statistical significance of associations. Previous research has examined the effect sizes related to associations between stressors and delay discounting behaviors. For example, meta-analysis of studies examining the relationship between individual experiences of stress, e.g. adverse life events, perceived stress, or allostatic load, and delay discounting found moderate to large effects (131). We are aware of only two previous published studies examining the relationship between an area-level measurement of area-level economic deprivation and delay discounting, both of which found that higher levels of area-level deprivation were associated with steeper delay discounting, and one of which reported effect sizes in the moderate range (132, 133). We are not aware of previous studies examining the relationship between structural stressors, defined as stressors reflecting mutually reinforcing systems that place individuals from some groups at a disadvantage, and delay discounting.

The studies described above did not include neuroimaging. While many neuroimaging studies do not report effect sizes, moderate effect sizes have been found in the relationship between early childhood deprivation and brain volume in brain region including the IFG/insula and ACC (79, 81), and other studies have reported a relationship between neighborhood poverty and brain structure in dmPFC (83). Thus, given the exploratory nature of this study, and the paucity of previously reported effect sizes relating structural stressors, and delay discounting and neural correlates, we have used the existing literature to estimate that with *n* = 72 children we will be able to detect with 80% correlations at least as large as r = 0.35. This moderate effect size would provide evidence of a signal worth pursuing in the R33 phase.

All procedures described here are included in our study protocol, which was reviewed by the Columbia University IRB (protocol ID: AAAV4120; approved on 2/18/2025). Columbia University will act as the single IRB for the study, and both Columbia University and the University of Puerto Rico are recruitment sites for the study. For this pilot phase, we plan to invite 72 children (aged 11–14, 50% female, 50% from the South Bronx, 50% from Puerto Rico) to provide: home address history from the previous five years, substance use risk, BJW and magnetic resonance imaging (MRI) for brain structure and DD-related brain function.

Three inclusion criteria and two exclusion criteria will be ascertained before participants are enrolled in the study: Inclusion criterion 1. The child participant is a biological or non-biological child of a member of the original BYS sample. Inclusion criterion 2. The child participant is aged 11 to 14. Inclusion criterion 3. Parent/caregiver is between the ages of 18–65 in the continental US and 21–65 in Puerto Rico, where 21 is the age of majority. Exclusion criterion 1. The child participant has a major neurological disorder (e.g., seizure disorder) or cognitive impairment (e.g., moderate to severe Autism Spectrum Disorder, Intellectual Disability). Exclusion criterion 2. The child participant has MRI contraindications (e.g., irremovable metal on the body, pacemaker, braces, etc. For participants who meet inclusion and exclusion criteria and express interest in participating in the study, informed consent, assent and confidentiality are carefully explained to all eligible participants prior to asking parents to provide informed consent and children to provide informed assent.

We will be using a secure web-based central electronic data capture system the Research Electronic Data Capture (REDCap) for collection of interview data at both study sites. This electronic data capture system ensures the privacy and security of the data collected by meeting the Good Clinical Practice (GCP) guidelines and the following applicable Federal Regulations-Health Information Portability and Accountability Act (HIPAA). MRI data from both sites will be stored and processed on an enterprise-level web server via Xnat, an open-source imaging informatics software platform dedicated to imaging-based research.

Adolescent participants in NY and PR will be compensated $100 for participating in the MRI scan, will receive $10 as part of completing the DD task, and $100 for completing the interview, for a total of $210. Parents will also be compensated $100 for participating by providing interviews regarding their children.

### Statistical analyses

We will use generalized linear models (GLMs) using the SS composite variable as a predictor and brain structure in prefrontal regions of interest, DD-performance, neural correlates of DD performance and BJW as outcome variables. These GLMs will also control for family SUD factors, individual experiences of unfair treatment, age, sex, and the presence of a psychiatric diagnosis. Due to the importance of understanding SS alongside other negative exposures, our models will also include adverse childhood experiences, measured using a combination of parent and child report, gathered by interview.

Exploratory analyses will examine the role of each individual SS index on gray matter volume (e.g., the effect of area-level group differences in income alone) and will examine site differences (South Bronx vs. Puerto Rico) in the associations. Site differences may suggest site-specific approaches to prevention and intervention.

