Three distinct dual systems models describe diverging growth curves for the neurobiological systems underlying reward sensitivity and cognitive control across adolescence in into adulthood. The Dual Systems Model (96), the Maturational Imbalance Model (97), and the Driven Dual Systems Model (98) all propose that during early adolescence, the reward-sensitive VS develops relatively quickly compared to the slower development of prefrontal regions associated with cognitive control, and this mismatch in development is theorized to explain why adolescence is life stage characterized by increased in risky behaviors, including substance use (98–105). The three dual systems models differ in their hypotheses regarding the growth curves of reward sensitivity and cognitive control during later adolescence and early adulthood, suggesting different outcomes during these later life stages (96–98). However, all three models agree that studying neural activity in reward-sensitive brain regions and prefrontal regions associated with cognitive control can contribute to our understanding of adolescent reward-related decision-making (100). For all these reasons, the dmPFC, ACC, IFG/insula and VS regions are particularly important to study, at this developmental stage, in relation to substance use risk (98, 100, 102–105).

*The Boricua Youth Study: An opportunity to isolate the role of SS on substance use, by controlling for familial factors*.

The Boricua Youth Study (BYS) is an epidemiological study formed with the goal of better understanding the lived experiences of Puerto Rican individuals and their families living in two contexts: the island of Puerto Rico, and the New York City region of the continental US (106). BYS started in 2001 through a collaborative effort between NYSPI/Columbia University, led by [name], and the University of Puerto Rico, led by [name]. BYS originally recruited about 2,500 children and their families based on multistage probability household samples, representative of the two original target populations: Puerto Rican families in the South Bronx, NY and in the metropolitan area of San Juan, Puerto Rico. The original cohort of BYS children were aged 5–13 at the first wave of recruitment and data were collected over 3 Waves, between 2001–2004 (106). A fourth assessment wave, collected during young adulthood, was collected between 2013–2018 (107, 108).

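### The structural stressor score is shared by area and possibly by family, but the named GLMs and the detectable r = 0.35 make no allowance for clustering, so precision will be overstated if children share areas

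*Protocol article*

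**What the plan says.** All references are to the protocol article.

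- **Model.** Statistical analyses: "We will use generalized linear models (GLMs) using the SS composite variable as a predictor". The outcomes are brain structure, delay discounting, its neural correlates and belief in a just world. On adjustment: "These GLMs will also control for family SUD factors, individual experiences of unfair treatment, age, sex, and the presence of a psychiatric diagnosis". Adverse childhood experiences are added in the next sentence. Site appears only among the exploratory analyses. No random effect, cluster unit or robust variance is named.
- **Level of the predictor.** Under Measurement of SS, the income and education indices are computed "within each census tract (i) our participants live in". The violence component is measured "at the precinct-level, divided by the total precinct population".
- **Families.** The first inclusion criterion (in the text under Power analysis) is: "The child participant is a biological or non-biological child of a member of the original BYS sample". No limit of one child per family is given. The parent cohort came from "multistage probability household samples" in two areas (Background).
- **Power.** The Power analysis says that with n = "72 children we will be able to detect with 80% correlations at least as large as r = 0.35". It also says that the power analysis will "focus on effect size rather than statistical significance of associations".

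**The concern.** Children with the same tract and precinct have the same SS value, and children in one precinct share at least its violence component. Siblings would also share the parental covariates. For a predictor that is constant within clusters, any positive residual correlation within the cluster inflates the true variance of its coefficient by the full design effect. A model that treats the children as independent does not see this.

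Residual correlation is plausible here. Tracts and precincts lie within one of two sites, and site is not in the main covariate list. Any site difference in an outcome that the covariates do not explain would therefore appear as correlation within areas.

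At stake are the reported intervals and p-values for SS, and the claim about what 72 children can detect.

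**Working it through.** **Inputs from the article:** n = 72, power 80%, r = 0.35. Alpha is not stated; 0.05 two-sided is assumed. The main models have about 9 covariate terms: 4 family SUD factors, unfair treatment, age, sex, psychiatric diagnosis and adverse childhood experiences. ADHD medication makes about 10 in the neural models.

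**Inputs assumed:** cluster size m and residual ICC. The article gives neither.

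**Step 1: the plan's own figure.** By Fisher z, detectable r = tanh[(1.960 + 0.842)/√(n − 3 − k)], where k is the number of covariates.

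- k = 0: tanh(2.802/√69) = 0.325. Power at r = 0.35 is 85.9%, and 62 children would suffice.
- k = 10: tanh(2.802/√59) = 0.349. Power at r = 0.35 is 80.2%.

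So 0.35 is matched almost exactly by 72 independent children and 10 covariates. With no covariates there is some slack: 72/62 = 1.16, which could absorb a design effect of that size or a loss of about 14% of children. The article does not say that the slack is meant for clustering, and the covariates alone use it up.

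**Step 2: effect of clustering.** Design effect DE = 1 + (m − 1) × ICC; effective n = 72/DE; type I error = 2 × [1 − Φ(1.96/√DE)]; detectable r as in Step 1 with k = 0 and effective n in place of n.

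| Assumption | DE | Effective n | Type I error | Detectable r (k = 0) |
|---|---|---|---|---|
| One child per area | 1.00 | 72 | 5% | 0.325 |
| m = 3, ICC 0.05 | 1.10 | 65.5 | 6.2% | 0.34 |
| m = 3, ICC 0.20 | 1.40 | 51.4 | 9.8% | 0.38 |
| m = 6, ICC 0.05 (upper bound) | 1.25 | 57.6 | 8.0% | 0.36 |
| m = 6, ICC 0.20 (upper bound) | 2.00 | 36.0 | 16.6% | 0.45 |

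For m = 3, power at r = 0.35 falls from 85.9% to 82.3% (ICC 0.05) or 72.0% (ICC 0.20). If k = 10 is kept, detectable r moves from 0.35 to 0.37 or 0.42.

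**Step 3: why m = 6 per precinct is an upper bound.** Only one of the three SS components is constant within a precinct. For a predictor that is only partly shared, DE = 1 + (m − 1) × ICC_x × ICC_y, where ICC_x is the predictor's own intracluster correlation. With equal weights, uncorrelated components and precinct-mates in different tracts, ICC_x = 1/3. Then:

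- ICC_y = 0.05: 1 + 5 × (1/3) × 0.05 = 1.08, type I error 6.0%, detectable r 0.34.
- ICC_y = 0.20: 1 + 5 × (1/3) × 0.20 = 1.33, type I error 9.0%, detectable r 0.37.

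Correlated components would fall between these figures and the upper bound.

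**Step 4: simulation check.** Ordinary least squares, 72 children, predictor constant within cluster, 4,000 runs per setting.

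- All children alone in their cluster: type I error about 5% at any ICC.
- 24 clusters of 3: 6.5% at ICC 0.05, 7.1% at 0.10 and 12.0% at 0.30.
- 12 sibling pairs plus 48 single children: 5.5% at ICC 0.3 and 7.3% at ICC 0.5.

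The formula and the simulation agree in direction and size. Siblings alone matter little; shared areas could matter more.

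**Step 5: the progression rule.** Progression needs r > 0.30. By Fisher z, the chance that one r exceeds 0.30 when the true r is 0 is 0.5% at n = 72, 0.7% at effective n 65.5 and 2.2% at effective n 45 (for example m = 4, ICC 0.20: 72/1.6).

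**The case against.** **The variance estimator is not stated.** A GLM can carry cluster-robust errors, and a condensed article may leave that to a fuller document. This stands as far as it goes: a reader might infer that the article commits to independent errors, and it does not say so. But the article does set out its model and publish a power figure, and neither makes a stated allowance for shared areas.

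**Clustering is not shown to occur.** Nothing says how many of the 72 children share a tract, precinct or family. The participants are the generation after a cohort first sampled in 2001 to 2004. Five-year address histories, if they feed the score, may break simple nesting. Siblings are permitted but not stated to be enrolled, and both would have to be aged 11 to 14. This stands, and it makes the point conditional. A reader might infer that the standard errors are bound to be too small; the documents do not support that.

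**The decision rests on a point estimate.** The pilot emphasises effect size, and r > 0.30 uses no standard error. This also stands. A reader might infer that clustering invalidates the decision to progress. It does so only indirectly, by making r noisier, and Step 5 shows that the change is small in absolute terms.

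**Conclusion.** The point holds in conditional form. The predictor is defined at area level, siblings are not excluded, the named models have no clustering term, and the detectable r carries no stated design effect. If children share SS values and residual correlation is positive, the precision of the SS estimates and the detectable r are both overstated.

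Under the assumption of 3 children per SS value and ICC 0.05 to 0.20, true standard errors are about 5 to 18% larger than reported (√1.10 to √1.40). The design effects of 1.25 to 2.0 for 6 children per precinct should be read only as an upper bound. If every child is alone in an area and family, or the residual ICC is zero, there is no error. What is affected is reported precision and the power statement; the go decision is not directly affected.

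**What to change.** 1. Keep the GLMs, but base SS inference on cluster-robust standard errors with a small-sample correction (CR2 with Satterthwaite degrees of freedom). Alternatively, use random intercepts for area and family where they can be estimated; if most areas hold one child, they may not be. Name the cluster unit and say how a child with several addresses is assigned.
2. Report a cluster-bootstrap interval beside the r used for progression. The threshold itself need not change.
3. Restate the detectable r over a plausible range of design effects, with the assumed number of children per tract, precinct and family.

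The cost is wording and a short recalculation. Intervals become somewhat wider and the detectable r slightly less favourable. Recruitment need not be restricted, because the analysis can handle any siblings who enrol.
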